### 8.1.2 Control Intervention (standard/routine/comparator)

The current local protocols for glycaemia control and nutrition management will be used in the control group and in the historical control group for comparison.

After ICU admission, a BG measurement is performed. If glycaemia is in the accepted range (5.0-8.5 mmol/l) or spontaneously normal (4.0 to 5.5 mmol/l), no correction is proposed. In this case, a BG control should be done every 2 hours. In case BG measurements are twice  $> 8.5$  mmol/l, a new control is proposed in another sampling site. If the BG measurement is still  $> 8.5$  mmol/l, an IV insulin-therapy should be initiated following the local protocol. A further BG control should be done within the next 15-30 minutes until stability of the BG. Then, BG controls should be done every 2 hours. If BG measurement are  $< 4$  mmol/l, insulin-therapy should be stopped (if in progress) and a correction can be performed. A new control is done within 15 minutes. If the glycaemia is still under 4, a new correction is done. If the glycaemia is spent above 4, BG control are spaced to every 30 minutes. Then, when the glycaemia spent above 5, BG control are done every 2 hours. The algorithm of the local glycaemia control ICU protocol is presented in Figure 9.

[figure not shown]

Figure 9. Algorithm of the local glycaemia control ICU protocol (control and historical control group)

An estimation of caloric target is performed after the admission in the ICU. Then, if the patient stays more than 4 days and if the indirect calorimetry measurement is achievable, the measurement is performed, and the caloric target is adjusted. If gastro-intestinal tract is functional and there are no contraindications to enteral nutrition, it is started from day 1 with an appropriate solution regarding the pathologies and with an initial debit of 25 ml/h or 10 ml/h for a patient with severe shock (can be adapted according to tolerance). The 80-100% of the energy target need to be achieved at the end of day 3. If the energy target (80-100%) is not covered at day 4, a SPN (Supplemental Parenteral Nutrition) is indicated to cover the target.

If enteral nutrition is contraindicated, a parenteral nutrition can be initiated in a progressive way. It can be either by a central venous access or by a peripheral one. Vitamins and trace elements should be supplemented with 1 ampoule of Addaven® and 1 ampoule of Cernevit®. Glutamine supplements can also be added on a case-by-case basis. If tolerance is good, PN is progressively increased to achieve 80-100% of the energy target by the end of day 3. The algorithm of the local ICU nutrition management protocol is presented in Figure 10.

[figure not shown]

*Figure 10. Algorithm of the local ICU nutrition management protocol (control and historical control group)*

### **8.1.3 Labelling and Supply (re-supply)**

GS2 will be installed in all bedside computers of the ICU by the IT manager of the ICU. The downloaded SW package will have the version number in the filename. Further information and labelling can be found on the GS2 Login page. A complete User Manual or Instructions for Use (IFU) will be supplied as a pdf-file.

### **8.1.4 Storage Conditions**

Not applicable.

## **8.2 Discontinuation or modifications of the intervention**

According to section 8.1.1 (Experimental Intervention (medical device)), the users of GS2 always have the option to accept GS2 advice, to accept it with modification or to refuse it. In this context, there are no situations in which the intervention will be discontinued or modified. As explained in point 7.4, the intervention of a patient is discontinued in case of death; withdrawal of life support; or consent withdrawal.

## **8.3 Compliance with clinical investigation intervention**

Some strategies to improve adherence to the use of GS2 will be made.

**Training:** All caregivers will participate in training sessions before the beginning of the study. They will also receive a summary brochure with the main information. During the trial a clinical investigator will come daily to see if the caregiver has any question and if there is a need for a one-to-one training.

**To do list:** GS2 contains a "To do list" as a reminder for the caregivers to use the system. The non-compliance will not be analysed while the study is underway. The rate will be analysed at the end of the study as a secondary outcome and will be defined as:

- Number of episodes per patient and in the cohort where a BG measurement is not followed up within 30 minutes by a request for GS2 advice.
- Number of episodes per patient and in the cohort where pumps were not set within 30 min according to a GS2 advice accepted by the nurse (nurse did not notice, was busy, forgot, or misinterpreted advice = true errors)

## **8.4 Data Collection and Follow-up for withdrawn subjects**

The medical follow-up of withdrawn subjects, or of subjects that drop out from the investigation prematurely is described in chapter 9.2.5 and chapter 9.2.6.

## **8.5 Clinical investigation specific preventive measures**

No medications or treatments are prohibited during the study. The use of medications that play a role in glycaemic control will be recorded in the CRF.

## **8.6 Concomitant Interventions (treatments)**

Apart from insulin therapy and nutritional therapy, all the medications and treatments will follow the usual practice in the ICU-HUG.

## **8.7 Medical Device Accountability**

Installation of the GS2 software on HUG's bedside computer stations will follow the procedure described in the Investigator's Brochure. A record of every installation (one installation per bedside computer) is made (See Integration Test Report Template, Appendix 6.) and kept at HUG-ICU. A copy of the report and a copy of the installation log file from every PC will be sent to the Manufacturer prior to the start of the clinical investigation.

Uninstallation of the GS2 software on HUG's bedside computer stations will be conducted by the HUG-ICU IT-manager. A record of every uninstallation is made by updating the information in the Integration Test Report. A copy of the report will be sent to the Manufacturer after conclusion of the clinical investigation.

## **8.8 Return, Analysis or Destruction of the Medical Device**

All data recorded in the central GS2 Database will be transferred in coded form to HUG's secuTrial® data repository. This transfer is done as the data becomes available or at the end of the study. Once the Monitor has completed its inspection, the IT manager of the ICU will delete the central GS2 Database and remove GS2 from the bed-side computers of the ICU-HUG.

In case of device deficiencies, including malfunction, usability issues, or inadequacy in the information supplied by the manufacturer including labelling, the log file will be sent to the manufacturer for analysis.

## 9. CLINICAL INVESTIGATION ASSESSMENTS

### 9.1 Clinical investigation flow chart(s) / table of clinical investigation procedures and assessments

[figure not shown]

## 9.2 Assessments of outcomes

### 9.2.1 Assessment of primary outcome

Time-in-target (range: 5.0 to 8.5 mmol/l) per patient and in the cohort:

- All the BG measurement will be recorded with the time of the measurement in the eCRF. Then the time spent in the target (5.0 to 8.5 mmol/l) will be calculated in percentage for each patient and for each of the patient groups.

### 9.2.2 Assessment of secondary outcomes

Glycaemic “variability”:

Mean and SD of BG

- All BG measurement will be reported in the eCRF daily. The mean BG with SD will be calculated from those data.
- Maximum of daily BG difference

Achievement of nutritional targets.

The protein goal is met (e.g., 80-100% of the accumulated target)

- In the control group, the total intake of protein per day is going to be reported in the eCRF. Then, it is going to be compared with the daily target and the percentage will be made. The mean percentage for the duration of the study will then be calculated.
- In the intervention group, the comparison between the daily intake and the daily target is carried out automatically by GS2. The percentage will be reported directly in the eCRF. The mean percentage for the duration of the study will when be calculated.

The caloric goal is met (e.g., 80-100% of the accumulated target)

- In the control group, the total intake of energy per day is going to be report in the eCRF. Then, it is going to be compared with the daily target and the percentage will be made. The mean percentage for the duration of the study will when be calculated.
- In the intervention group, the comparison between the daily intake and the daily target will be made automatically by GS2. The percentage will be directly report in the eCRF. The mean percentage for the duration of the study will then be calculated.

Energy debt at the end of the stay

- In the control group, the total intake of energy per day is going to be reported in the eCRF. The daily energy target will be reported every day as well. Then the total energy debt is calculated as the addition of the daily difference between the energy target and the energy intake.
- In the intervention group, the energy debt will be directly calculated and extracted from GS2.

Protein debt at the end of the stay.

- In the control group, the total intake of protein per day is going to be reported in the eCRF. The daily protein target will be reported every day as well. Then, the total protein debt will be calculated as the addition of the daily difference between the protein target and the protein intake.
- In the intervention group, the protein debt will be directly calculated and extracted from GS2.

### 9.2.3 Assessment of other outcomes of interest

Workload:

Frequency of BG measurements per patient and in the cohort

- All the BG measurements will be daily reported in the eCRF. The mean number of BG measurements with standard deviation (SD) will be calculated per patient and in the cohort.

Frequency of adjustments of insulin and nutrition pump settings

- All the insulin adjustments will be daily reported in the eCRF. The mean number of insulin adjustments with SD will be calculated per patient and in the cohort.

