| Outcome(s): | 
Primary outcome:
Time-in-target (BG in range: 5.0 to 8.5 mmol/l) per patient and in the cohort.
 
Other outcomes:
Concerning safety:
 
Hypoglycaemia
 
 
- Overall number and percentage of mild (<math>\leq 3.2</math> mmol/l), and severe (<math>\leq 2.2</math> mmol/l) hypoglycaemic events per patient and in the cohort
 
- Number and percentage of mild (<math>\leq 3.2</math> mmol/l), and severe (<math>\leq 2.2</math> mmol/l) hypoglycaemia events due to non-compliance (only in intervention arm)
 
 
Hyperglycaemia (> 8.5 mmol/l)
 
 
- Time to normalize blood glucose (2 values between 5.0 and 8.5 mmol/l as indicator for normalization)
 
- Percentage of time in the ICU with hyperglycaemia (BG > 8.5 mmol/l) before and after normalization per patient and in the cohort
 
- Percentage of time in the ICU with hyperglycaemia (BG > 8.5 mmol/l) before and after normalization per patient and in the cohort due to non-compliance (only in intervention arm)
 
- Number of hyperglycaemic episodes after normalization per patient and in the cohort
 
- Number of hyperglycaemic episodes after normalization per patient and in the cohort due to non-compliance (only in intervention arm)
 
 
Non-compliance (only in intervention arm)
 
 
- Number of episodes per patient and in the cohort where a BG measurement is not followed up within 30 minutes by a request for Glucosafe 2 advice.
 
- Number of episodes per patient and in the cohort where pumps were not set within 30 min according to a Glucosafe 2 advice accepted by the nurse (nurse did not notice, was busy, forgot, or misinterpreted advice = true errors)
 
- Number of advices given by GS2 which were accepted, accepted with modification, or rejected
 
 
Concerning effectiveness:
 
Achievement of nutritional goals.
 
 
- The protein goal is met (e.g. 80-100% of accumulated target)
 
- The caloric goal is met (e.g. 80-100% of accumulated target)
 
- Energy debt at the end of the stay
 
- Protein debt at the end of the stay
 
 
Workload:
 
 
- Frequency of BG measurements per patient and in the cohort
 
- Frequency of adjustments of insulin and nutrition pump settings
 
 
Glycaemic "variability":
 
 
- Mean and standard deviation (SD) of BG
 
- Maximum of daily BG difference
 
 
Prediction of blood glucose:
 
Prediction error as a function of time elapsed since last BG measurement, per patient, per cohort.
 |

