| Measurements and procedures: | 
Screening will be done every day (Monday to Friday). Eligible patients will be randomly allocated to either intervention or control group. Before inclusion, all patients will be treated according to the ICU- Geneva Protocols.
 
Collected data:
 
Baseline at study inclusion day
 
 
- Body mass, height and body mass index (BMI)
 
- Age, gender
 
- Date and time of admission in the ICU
 
- Primary diagnostic
 
- Known chronic illness (diabetes, acute kidney injury (AKI), pancreatitis, tumor, etc.).
 
- Medication influencing glycaemia (oral antidiabetics' insulin, steroids, prednisone, etc.).
 
- Renal and hepatic status
 
- Glycaemia and lactate
 
- Vitals
 
- Severity score (APACHE II, SAPS II) at ICU admission
 
 
Daily data from inclusion day (maximum follow up of 15 days)
 
When possible – Following routines measurement.
 
 
- Glucose measurements
 
- Other laboratory: lactate, CRP, sodium (Na), potassium (K), glycohemoglobin (HbA1C), urea, creatinine, glomerular filtration rate (GFR), protein, albumin, ASAT, ALAT, phosphatase alkaline, γ-glutamyltranspeptidase (GGT), bilirubin
 
- Any events (intubation, extubation, length of surgery, infusions, cardiac events, infections, requirement for red blood cell (RBC) transfusion, hemodynamic rate (HR), organ failure)
 
- Vitals (blood pressure, temperature, heart rate etc.)
 
- Antibiotics usage
 
- Vasopressor
 
- Steroids
 
- Propofol® for sedation
 
- Glucose perfusion
 
- Insulin therapy including boluses.
 
- Body weight, BMI, Ideal body weight (if needed), presence of oedema.
 
- Energy expenditure (IC or predictive formula)
 
- Energy and protein targets over the day
 
- Prescription and administration (ml of product, kcal and grams of protein).
 
- Daily water balance
 
- Diuresis
 
- Diarrhoea, constipation
 
- Nausea, Vomiting, gastric residual
 
- Physical therapy
 
- Medical Research Council Scale (MRC Scale)
 
 
Upon ICU leave
 
 
- Duration of ICU stay
 
- MRC Scale at ICU discharge
 
- Alive status at ICU discharge
 
- Duration of hospitalization
 
- Alive status at hospital discharge
 
- BMI at hospital discharge
 
 |

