### 5.3 Other Outcomes of Interest

Workload:

- Frequency of daily and cumulated BG measurements per patient and in the cohort during the patient's enrolment period (duration of the ICU stay with a max of 15 days).
- Frequency of daily and cumulated adjustments of insulin and nutrition pump settings during the patient's enrolment period.

Compliance (only in intervention arm)

- Number of episodes per patient and in the cohort where a BG measurement is not followed up within 30 minutes by an accepted GS2 advice (during the enrolment period)
- Number of episodes per patient and in the cohort where GS2 advice was accepted by the nurse but pumps were not set according to the advice within 30 min by the nurse (nurse did not notice, was too busy, forgot, or misinterpreted advice = true errors)
- Number of advices given by GS2 which were accepted, accepted with modification or rejected

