## Advising on nutrition and insulin therapy.

Advice on insulin and nutrition is required every time a new BG measurement becomes available. On the GS2 "Advice" page the user is reminded when the next BG measurement is due. In the example in Figure 7, this is in -30 min, or in other words, the measurement is 30 min overdue. The user should respond by making a BG measurement and reporting it to Centricity. Within 10s GS2 will have imported the measured BG and will replace the "To do" item "BG measurement due" with a new "To do" item "Request new advice".

[figure not shown]

Figure 7. The GS2 "Advice" page which is used to request advice. The page displays the history of insulin therapy, the BG measurements, and simulated and predicted BG (black curve) in the diagram at the top left. The nutrition history is displayed in the bottom left diagram. On the right-hand side, the upper panel shows the current insulin sensitivity of the patient, current "To do" items (user tasks) and when they are due or overdue. Finally, the lower right-hand panel displays the current state of achievement of the caloric and protein intake targets with respect to the ongoing nurse shift, and for the entire day in the ICU.

The user can request advice by clicking the face icon on the middle-left bar. GS2 then shows the advice pop-up (Figure 8). In the example given below, GS2 advises to reduce enteral nutrition (Novasource® GI Forte) from the current rate of 45 ml/h to 35 ml/h. It also recommends starting an amino acid supplement in the form of 15 ml/h Dipeptiven® and stopping the glucose infusion. The advised insulin dose remains unchanged at 1 U/h. The right-side panels show that both the caloric and protein targets are being met. The user can choose to explore other treatment options, or click on "Accept Choice". The user must then set the pumps according to the advice and report the pump settings to Centricity.

[figure not shown]

Figure 8. The GS2 Advice pop-up window, which displays the recommended pump rates for the nutrition and insulin pumps. The two panels on the right display the achievement of calorie and protein targets that were achieved in the figure.

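### Section 9.2.3 counts insulin adjustments only, although the workload outcome is defined as adjustments of insulin and nutrition pump settings

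*Protocol*

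**What the plan says.** Three places in the protocol name the outcome in the same way. The synopsis, under workload, lists "Frequency of adjustments of insulin and nutrition pump settings". Section 5.3 lists "Frequency of daily and cumulated adjustments of insulin and nutrition pump settings during the patient's enrolment period". Section 9.2.3 repeats the synopsis wording as a sub-heading.

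The operational text under that sub-heading has two sentences: "All the insulin adjustments will be daily reported in the eCRF. The mean number of insulin adjustments with SD will be calculated". Nutrition pumps appear in neither.

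Nutrition data are mentioned elsewhere, but as amounts. The daily data list in the synopsis has "Prescription and administration (ml of product, kcal and grams of protein"), the investigation schedule has a row for energy and protein intake, and section 9.2.2 has total daily intake entered in the eCRF for control patients.

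Section 8.1.1 states that GS2 advice on both insulin and nutrition is needed at every new blood glucose measurement.

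**The concern.** The outcome has two components and the instruction for measuring it has one. This is not detail that a statistical analysis plan would normally supply. It is a collection and summary instruction that departs from the protocol's own definition, and an analysis plan cannot count what nobody was told to record.

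At stake is the meaning of the workload result. GS2 advises on nutrition together with insulin, so nutrition pump changes are something its advice can prompt. A figure reported as insulin and nutrition adjustments but built from insulin alone would be mislabelled. If nutrition changes were later added from the GS2 database for the intervention group only, the groups would be counted from different sources. Workload also matters to the protocol's reasoning: section 8.1.1 gives higher workload as the reason for stopping on a large prediction error, although in the context of how often glucose is measured.

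**Working it through.** No statistical figure is involved, so the check sets the sections side by side.

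**Step 1. Definition against rule.**

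| Place | Insulin pumps | Nutrition pumps | Form of result |
|---|---|---|---|
| Synopsis, workload | yes | yes | frequency |
| 5.3 | yes | yes | frequency, daily and cumulated |
| 9.2.3, sub-heading | yes | yes | frequency |
| 9.2.3, what is recorded | yes | no | daily entry in the eCRF |
| 9.2.3, what is summarised | yes | no | mean and SD, per patient and cohort |

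Nutrition is missing from both the recording and the summary sentence. The cumulated form asked for in 5.3 is not mentioned in 9.2.3 either.

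**Step 2. Does another section supply the missing count?**

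- Synopsis, daily data list: amounts prescribed and given. It names no count of rate changes, and a daily total does not show how many changes produced it.
- Investigation schedule: energy and protein intake only.
- 9.2.2: daily intake and percentage of target, taken from GS2 in the intervention group and from eCRF totals in the control group.
- 9.2.3, non-compliance: accepted advice not carried out within 30 minutes, intervention group only. This counts omissions, not adjustments.
- 8.1.1 and 8.8: in the GS2 workflow the user reports pump settings to Centricity, and GS2 data are transferred to secuTrial. This is a possible source for the intervention group, but no counting rule is attached to it.
- 8.1.1 describes creating a patient in GS2 for those randomised to the intervention group. It describes no such step for randomised controls.

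No section states how nutrition pump adjustments are recorded or counted in any group.

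**Step 3. The protocol's own example.** In the worked advice in 8.1.1, the enteral rate goes from 45 to 35 ml/h, an amino acid supplement is started at 15 ml/h and the glucose infusion is stopped. On insulin the text says: "The advised insulin dose remains unchanged at 1 U/h".

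- Count under 9.2.3 (insulin only): 0.
- Count under 5.3 (insulin and nutrition): at least 1 for the enteral change. It is up to 1 + 1 + 1 = 3 if the amino acid start and the glucose stop also count as nutrition pump adjustments, which the protocol does not define.

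The same episode scores 0 under the rule and between 1 and 3 under the definition. This is one illustration of an advice, not a rate, and cannot be scaled to a group mean.

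**The case against.** The strongest reply is that this is a dropped word. The sub-heading in 9.2.3 still names nutrition pumps, the eCRF templates listed in 12.1.1.1 are not shown, and the daily data list is not itemised: it has no count of insulin adjustments either, yet 9.2.3 says these are recorded. Its nutrition entry might include prescribed rates. Intervention-group pump settings are reported to Centricity. GS2 uses nutrition as a model input, and its prediction error is to be estimated on the historical group, so some nutrition history must be retrievable there.

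Much of this stands, and it limits the point in three ways.

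- A reader might infer that nutrition adjustments are never captured, or that no control value can exist. The documents do not show that. They show only that no recording or counting rule is stated. For the randomised controls they do not say whether rate changes are charted.
- A reader might infer that GS2 adds nutrition workload and that an insulin-only count understates it, so that a finding of equal or lower workload would be false. The documents give no nutrition pump workload for either arm. Standard care in 8.1.2 also changes nutrition, with a starting rate adapted to tolerance and a progressive increase, and a GS2 advice need not change a pump.
- The outcome is of lower rank. It sits under other outcomes of interest, no objective in section 4 names workload, and glucose measurement frequency, the other workload measure, has its own recording and summary rule.

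The reply does not remove the mismatch. Whatever the intention, the only instruction given fails to deliver the outcome defined.

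**Conclusion.** The point holds as an inconsistency between a defined outcome and its assessment rule. Followed literally, 9.2.3 produces an insulin-only count that misses nutrition changes of the kind GS2 advice can prompt. The direction and size of any resulting difference between groups cannot be judged from the protocol.

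This rests on the protocol text alone; the eCRF templates could show that the item is already captured, in which case only the wording of 9.2.3 and the source for each group need correcting. The matter should be corrected, but it is modest: the primary outcome, the sample size and the safety outcomes are not touched.

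**What to change.** Amend 9.2.3 as follows:

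1. State that both insulin and nutrition pump adjustments are recorded and counted.
2. Give one definition of an adjustment for all groups, for example a start, a stop or a rate change, and say which infusions count as nutrition (enteral, parenteral, amino acid, glucose).
3. Name the source for each group. Where charting allows, use the same ePDMS (Centricity) extraction in the intervention, control and historical groups. That rate changes are charted there for the two control groups is an assumption to confirm first; if they are not, say so and state what can be compared.
4. Report insulin and nutrition adjustments separately and combined, daily and cumulated as in 5.3.
5. Add nutrition pump adjustments to the daily data list in the synopsis.

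The cost is a small extra data extraction and a short text change. No clinical rule changes.
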